### Phase II: designing interventional program

During the study's second phase, we will undertake a two-step process to formulate an intervention that addresses the needs and apprehensions of women considering cosmetic surgery for their genital area. These steps involve:

#### Textual analysis and review

This stage is the primary prioritization of concerns and the development of appropriate interventions**.** In the second phase, we will assess interventions and programs related to the needs and concerns associated with GCS, both in Iran and other countries. To ensure a comprehensive search, we have utilized various databases, such as SID, Magiran, Iran Medex, ProQuest, PubMed, Web of Science, Scopus, Sage, and Embase. Our investigation encompasses the period from the year 2000 up to September 2023. We have conducted database searches using diverse combinations of keywords in both Persian and their corresponding Latin equivalents. These keywords encompass "genital cosmetic surgery," "sexual health," "women," "labiaplasty," "genital self-image," "qualitative research," "mixed method," "female," "anesthetic surgery," and "genital self-image."

#### Conducting an expert panel discussion

Based on the first-stage research findings, the panel of experts will prioritize identified needs and concerns. The development of the intervention will heavily rely on the opinions of these experts, with a focus on the most crucial interventions and programs. Before convening the expert panel meeting for the target group, the research team, guided by esteemed professors and advisors, will define the goals and initial content of the interventions addressing these needs and concerns. Subsequently, the preliminary format of the designed interventions will be presented to the experts during the panel meeting. During this meeting, experts will prioritize the identified needs and concerns concurrently. The highest quality intervention will then be implemented in the quantitative phase. An expert meeting will be organized and conducted as a nominal group, and small group discussions (Focus Groups) will be structured to address this. This meeting will involve experienced experts with a history of providing services in sexual and reproductive health, specifically women's health. The participants will include specialists in reproductive health, psychiatrists, gynecologists, midwives, nurses, and psychologists.

Utilizing the Focus Group approach is essential, as it facilitates the extraction of diverse ideas and opinions and encourages collective thinking. This approach is precious in shaping the intervention to address concerns related to women seeking cosmetic surgeries for the genital system.

The Template for Intervention Description and Replication (TIDieR) tool will assess the designed intervention [17]. Given the need for a comprehensive intervention description to make informed selections, we will utilize the TIDieR checklist and model guide to detail and replicate the intervention. The TIDieR checklist comprises 12 essential items:Brief name: provides a succinct name or phrase describing the intervention.Why: explains the underlying logic, theory, or purpose of essential intervention components.What (materials): describes any physical or informational materials used in the intervention, including those provided to participants or used in its delivery.What (procedure): details the location, strategies, activities, and processes involved, including any supportive activities.Who provided: specifies the expertise, background, and specific training of intervention providers.How: describe the delivery methods (e.g., face-to-face or online) and whether they are individual- or group-based.Where: identifies the locations where the intervention occurs, including necessary infrastructure.How much: addresses the intervention's quantity or dose.When: specifies the frequency of the intervention.Tailoring: focuses on customizing intervention details, such as session duration, frequency, and intensity.Modification: describes any adaptations or changes made during the study, including reasons, timing, and implementation.How well (planned): discuss methods for assessing adherence to the intervention and strategies for maintaining or improving compliance.

The checklist enhances the reporting process and repeatability of interventions, ensuring that the most suitable intervention is selected through quantitative evaluation by a group of experts. Before this research's quantitative stage, 8 to 10 field experts will complete and review the checklist to assess the intervention thoroughly.

### Phase III: quantitative study

#### Type and approach

In the quantitative phase of this mixed-method research, a semi-experimental trial will be conducted, comprising both intervention and control groups. This phase, the second stage of the study, will primarily concentrate on the quantitative aspect, specifically the intervention test.

The third stage of this research involves a quantitative clinical trial. Its objective is to evaluate the effectiveness of the intervention designed to address the needs and concerns of women seeking cosmetic surgery for the genital system.

#### Population

In this study stage, the participants will be chosen from married women aged 18–49. These women will attend women's clinics at hospitals affiliated with Tabriz University of Medical Sciences and Tehran University of Medical Sciences.

#### Inclusion criteria

To participate in the trial phase of the study, individuals must meet the following criteria:Absence of physical or mental illnesses or the use of specific medicationsPossess minimal literacyExpress a desire to take part in the studyNot be pregnantNot be breastfeeding

#### Exclusion criteria

Participants will be excluded from the quantitative phase of the study if they meet any of the following criteria:Congenital disabilities of the genital system.History of burns or cancer in the genital area.Various degrees of female circumcision.Confirmed sexual dysfunction (FSFI ≤ 26).Multiple degrees of pelvic organ prolapse.Non-cooperation of participants in continuing to attend training sessions.Occurrence of pregnancy during the course.

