#### Sampling method and randomization

The researcher will initiate the process by obtaining ethical approvals from the Tehran University of Medical Sciences. Following this, they will secure the required legal documents and permits from the Medical Vice-Chancellor of Tabriz and Tehran Universities of Medical Sciences. If necessary, this will allow them to conduct sampling within hospitals, clinics, and facilities under the university's jurisdiction, including private properties.

Subsequently, the researcher will visit the gynecological clinics within these facilities. In collaboration with the department head and resident urogynecology specialist, they will identify individuals seeking GCS within this clinical setting.

The initial sampling will employ a convenience sampling method, with individuals expressing an interest in participating in the study. They were subsequently screened against the eligibility criteria. Eligible participants will then be categorized into two groups: the intervention group, which will receive education tailored to address genital area needs and concerns, and the control group, which will receive sexual health and reproductive education.

An independent individual not involved in the research will generate an allocation sequence using a computer program (randomizer) to allocate participants. The allocation process will be concealed by writing the type of training assigned to each participant on paper, which will then be sealed inside consecutively numbered opaque envelopes.

Following the entry of each eligible participant into the Study (after obtaining informed consent and collecting primary data), the envelopes will be opened sequentially, and the participant will be assigned to a group according to the order of entry into the study.

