#### Participant recruitment and data collection

Upon identifying eligible participants, informed consent will be obtained, and the participants will proceed to complete the study questionnaires. Given that many genital cosmetic surgeries are conducted in hospitals and private clinics, the researcher will initiate sampling in these facilities after making the necessary arrangements in case access to potential participants in these settings is limited.

Following the intervention sessions in both the intervention and control groups, changes in the participants' awareness and attitudes regarding the decision to undergo cosmetic surgeries will be reassessed.

Regarding blinding, this study will employ one-way blinding. Due to the nature of the intervention, it is not feasible to blind the researcher or the participant. However, to ensure the blinding of the outcome assessor, the questionnaires will be administered and completed by the researcher's assistant.

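### Two post-randomisation events, stopping attendance and pregnancy during the course, are listed as exclusions from the trial phase, which can bias the comparison in an unknown direction

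*Protocol article*

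**What the plan says.** The Phase III section headed Exclusion criteria opens with "Participants will be excluded from the quantitative phase of the study if they meet any of the following criteria". Most items that follow are baseline conditions. Two are not: "Non-cooperation of participants in continuing to attend training sessions" and "Occurrence of pregnancy during the course".

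Under Sampling method and randomization, the envelope is opened "after obtaining informed consent and collecting primary data"; then "the envelopes will be opened sequentially, and the participant will be assigned to a group according to the order of entry into the study". The intervention arm receives education on genital needs and concerns, and the comparator is "the control group, which will receive sexual health and reproductive education". Participant recruitment and data collection says that "it is not feasible to blind the researcher or the participant", and places the reassessment after the sessions in both groups.

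The primary outcome is intention to have, or actual performance of, genital cosmetic surgery (GCS). FSFI and FGSIS are secondary. The Analysis approach section lists tests. Nothing in the article says that women excluded for these two reasons are still assessed or are analysed in their allocated group.

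**The concern.** An exclusion applied at screening does no harm to a randomised comparison. One applied after allocation can, because what triggers it may itself depend on the arm and on the outcome.

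Both conditions are possible here. The women know which programme they attend, the programmes differ, and every participant enters because she is seeking surgery. How firmly a woman is set on surgery may affect whether she keeps attending, and may do so differently in the two programmes. Pregnancy may change the decision about, or timing of, elective surgery, and may change the FSFI.

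The rule takes women out of the whole phase and not only out of training. If they are therefore not reassessed, no later analysis plan can restore them. With 17 women per group, two or three such removals are visible in the result.

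**Working it through.** **Timing.**
1. The Inclusion criteria already require that a woman is not pregnant at entry, so the pregnancy item in the exclusion list refers to pregnancy after entry.
2. Stopping attendance presupposes that sessions have begun. Allocation follows consent and baseline data, and decides which sessions she attends.
3. Outcome is reassessed after the sessions.

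Both events therefore fall between randomisation and outcome.

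**The plan's own figure.** Sample size: 15 per group with 10% dropout. 15 / (1 − 0.10) = 16.7, rounded up to 17, which reproduces. Ten per cent of 17 is 1.7, or about two women per arm. (Whether 15 follows from the stated means and SD is a separate question and does not affect this point.)

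**Primary outcome, one-arm case.** Assumptions, since the documents give no rates: no true effect; a proportion p in both arms still intends surgery; a fraction x of the intervention arm is excluded, all of them intenders; control loses no intenders selectively. The rate seen in the intervention arm is (p − x)/(1 − x), and the spurious benefit is x(1 − p)/(1 − x).

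| x | Rate seen, p = 0.7 | Spurious benefit, p = 0.7 | p = 0.5 | p = 0.9 |
|---|---|---|---|---|
| 10% | 0.6/0.9 = 66.7% | 3.3 points | 5.6 | 1.1 |
| 20% | 0.5/0.8 = 62.5% | 7.5 points | 12.5 | 2.5 |
| 30% | 0.4/0.7 = 57.1% | 12.9 points | 21.4 | 4.3 |

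In whole women, with 12 of 17 (70.6%) intending in each arm: removing 2, 3 or 5 intenders from the intervention arm leaves 10/15 = 66.7%, 9/14 = 64.3% or 7/12 = 58.3%. The spurious differences are 3.9, 6.3 and 12.3 points.

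**Opposite case.** If those excluded from the intervention arm are all non-intenders, the rate seen is p/(1 − x). At p = 0.7 this is 0.7/0.9 = 77.8% for x = 10% and 0.7/0.8 = 87.5% for x = 20%, which is 7.8 and 17.5 points against the intervention.

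**Effect on the test.** Simulation of 200,000 null trials, 17 per arm, p = 0.7, nominal 5% chi-square test:

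| Loss pattern | Mean difference (points) | Rejection rate |
|---|---|---|
| 10% at random, both arms | 0.0 | 5.5% |
| The same intender-only 10% loss in both arms | −0.1 | 5.5% |
| Intervention loses 10% (intenders), control 10% at random | −3.3 | 5.8% |
| Intervention loses 20% (intenders), control 10% at random | −7.6 | 7.7% |
| Intervention loses 30% (intenders), control 10% at random | −12.9 | 11.5% |

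**FGSIS (secondary), upper extreme.** If exactly the 2, 3 or 4 lowest scorers of 17 are lost from one arm and none from the other, simulated two-sided type I error is about 10%, 15% and 21%. The mean shifts are 0.205, 0.295 and 0.378 SD; multiplied by the plan's SD of 3.22 they are 0.66, 0.95 and 1.22 points. If dropout is only correlated with outcome (an assumption), the error rates are 5.5%, 5.8% and 6.3% at a correlation of 0.3, and 6.4%, 7.6% and 8.6% at 0.5.

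**The case against.** The tempting stronger reading is that the rule does bias the trial, and does so in favour of the intervention: committed women walk out of sessions that question surgery, and the receptive ones remain. The documents do not support that as a fact. The intervention content does not yet exist; it is to come from the qualitative phase and the expert panel, and the Background states its aim as well-informed decisions. No section describes sessions that argue against surgery. Control women also seek surgery, are also unblinded, and may also stop attending. A woman who has lost interest in surgery may leave too, and removing her counts against the intervention. Nothing suggests that pregnancy differs by arm. This part of the objection stands: direction and size are unknown.

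It also stands that the large figures need strong assumptions. At the protocol's own 10% dropout the one-arm case moves the primary by 3.3 points and barely changes the test's error rate. The FGSIS error rates need perfect selection in one arm on a secondary outcome.

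A further objection is that analysis populations commonly belong in a statistical analysis plan, which is not shown, and that a completers' analysis is inferred and not stated. That is fair about the analysis set, and its absence from the article is not the complaint. The exclusion rule, however, is written down and covers the whole quantitative phase. An analysis plan that kept these women would have to contradict it.

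**Conclusion.** The point holds as a defect in a stated rule. Two of the listed exclusions act after randomisation and before outcome assessment, and followed as written they remove randomised women for reasons that may relate to the primary outcome and may differ by arm. The comparison can be biased.

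Bias in favour of the intervention is plausible if committed women leave its sessions more often, but the documents do not establish it. On the assumption of 70% intention in both arms, the spurious benefit runs from about zero (equal, same-cause loss in both arms) through 3.3 points (10% of the intervention arm, all intenders) to 12.9 points (30%), and the sign reverses if non-intenders leave. The FGSIS error rates of about 10% to 21% are an upper extreme.

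**What to change.** Take both items out of the exclusion list and relabel them as discontinuation of training sessions. State that these women are still asked to complete the end-of-trial questionnaires. Make the main analysis one of all randomised women in their allocated group, and show attenders only as a supplementary analysis. For the primary outcome, add a sensitivity analysis that counts women without a final assessment as still intending surgery, which is their state at entry. This concerns follow-up and analysis only and prescribes nothing about clinical care.

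The cost is revised wording and some extra contacts on an intimate subject, some of which may fail. Including women who did not complete the training may dilute the effect estimate. The change needs to be in place before follow-up of such women is lost.

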#### Research sample

In this research stage, the sample will comprise married women who visit women's clinics at hospitals affiliated with Tabriz and Tehran Universities of Medical Sciences. These women have expressed concerns and anxiety about their genital area and are seeking cosmetic surgery for this specific concern.

#### Research environment

The research will be conducted in women's clinics within educational hospitals affiliated with Tabriz and Tehran Universities of Medical Sciences. In cases where access to eligible participants in government centers may be challenging, sampling from private sectors will be explored because most of these surgeries are performed in private centers. Additionally, posters will be displayed at epilation and laser hair removal centers to maximize participant recruitment, inviting individuals to participate in the study.

#### Sample size

The sample size for this study was determined using G-Power software, considering various aspects of genital self-image. Referring to the research conducted by Weitkamp et al. [18], with values M1 = 29.09, M2 = 24.11 (assuming a 20% increase due to the intervention's impact), SD1 = SD2 = 3.22, a two-sided α of 0.05, and a Power of 90%, the sample size for each group was initially computed as 15. The final sample size for each group was established at 17 individuals to accommodate a potential 10% dropout rate.

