#### Study variables and outcomes

After the trial phase, the following variables and outcomes will be examined:

Independent Variables (Educational Interventions): These are the interventions designed and implemented as part of the study.

Dependent Variable: The primary dependent variable is the decision to undergo or refrain from GCS, which will be assessed at the end of the trial phase.

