##### Primary outcomes

Intention to undergo or actual performance of genital cosmetic surgeries.

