##### Secondary outcomes.

Women's Female Sexual Function Index (FSFI) before and after the intervention.Women's Female Genital Self-Image Scale (FGSIS) before and after the intervention

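### The 90% power and 17 per group rest on mean genital self-image, a secondary outcome; no rate or power is given for the primary surgery decision, which would need a drop of roughly 40 to 60 points

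*Protocol article*

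**What the plan says.** The Sample size section of the protocol article opens: "The sample size for this study was determined using G-Power software, considering various aspects of genital self-image". The inputs are two means, "M1 = 29.09, M2 = 24.11", and a common SD of 3.22, with "a two-sided α of 0.05, and a Power of 90" percent. From these, "the sample size for each group was initially computed as 15". The section ends: "The final sample size for each group was established at 17 individuals to accommodate a potential 10% dropout rate".

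Under Study variables and outcomes, "The primary dependent variable is the decision to undergo or refrain from GCS", to be assessed at the end of the trial phase. The Primary outcomes entry reads: "Intention to undergo or actual performance of genital cosmetic surgeries". Genital self-image appears only under Secondary outcomes, as the "Female Genital Self-Image Scale (FGSIS) before and after the intervention". The Phase III Data collection process section gives that scale a range of 7 to 28. The Analysis approach section lists t-tests, analysis of covariance, chi-square, Fisher and Mann–Whitney tests without assigning any of them to an outcome.

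**The concern.** A power statement means something only for the outcome and effect it was computed for. Here the only calculation concerns a difference in means on a construct listed as secondary, yet it is offered as the basis for the whole study. For the decision about surgery, the article states no expected proportion in either group and no difference worth detecting.

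What is at stake is how the primary result will be read. A reader who sees 90% power and a non-significant primary result will tend to conclude that the education does not change the decision. With 34 women, a non-significant result would be compatible with a substantial effect. The control group also receives education (sexual and reproductive health), which could narrow the contrast.

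**Working it through.** **1. The plan's own figure.** Inputs from Sample size: difference 29.09 − 24.11 = 4.98; SD 3.22; standardised difference 4.98 / 3.22 = 1.547; two-sided alpha 0.05; power 90%.

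- Normal approximation: n = 2 × (1.960 + 1.282)² / 1.547² = 8.8, so 9 per group.
- Two-sample t-test (noncentral t): n = 9.85, so 10 per group.
- t-test power with these inputs is 98.3% at 15 per group and 99.2% at 17.
- Dropout: 15 / (1 − 0.10) = 16.7, so 17. This step reproduces.

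The stated 15 does not follow from the printed inputs. In addition, the first mean, 29.09, exceeds the maximum of 28 given for the FGSIS, so it cannot be a mean on that scale as described.

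**2. The primary outcome.** The decision is treated as binary, because it is worded as a choice between two courses and no graded scale is stated for it. The article gives no rates, so control rates of 70% to 100% are assumed. The high end is included because the Research sample section describes women who are already seeking surgery.

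Power is the sum, over all pairs of counts (x₁, x₂), of Bin(x₁; n, p₁) × Bin(x₂; n, p₂), for those pairs where the test rejects at two-sided 0.05. Each cell shows Fisher / uncorrected chi-square.

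15 analysed per group:

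| Control rate | Intervention rate needed for 90% power | Power, 30-point drop | Power, halving |
|---|---|---|---|
| 70% | 9.6% / 15.0% | 22.7% / 37.0% | 32.2% / 48.0% |
| 80% | 18.0% / 24.0% | 24.6% / 41.9% | 44.7% / 62.7% |
| 90% | 29.5% / 37.8% | 32.5% / 51.0% | 64.1% / 81.0% |
| 95% | 38.7% / 47.4% | 39.6% / 57.7% | 78.1% / 89.9% |
| 100% | 53.6% / 60.7% | 48.5% / 70.3% | 94.1% / 98.2% |

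Subtracting the second column from the first gives the drop needed: 46.4 to 62.0 points by Fisher and 39.3 to 56.0 points by chi-square.

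17 per group with no losses:

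| Control rate | Intervention rate needed for 90% power | Power, 30-point drop | Power, halving |
|---|---|---|---|
| 70% | 13.9% / 18.7% | 31.3% / 45.0% | 42.9% / 57.4% |
| 80% | 23.4% / 28.6% | 31.9% / 45.6% | 56.1% / 69.9% |
| 90% | 34.9% / 40.4% | 39.2% / 52.9% | 73.4% / 83.8% |
| 95% | 43.6% / 49.5% | 48.0% / 63.0% | 85.1% / 91.9% |
| 100% | 58.4% / 64.8% | 61.1% / 79.8% | 97.5% / 99.4% |

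For 20-point drops at control rates of 70% to 90%, power with 15 per group is 10% to 15% by Fisher and 20% to 28% by chi-square.

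**The case against.** **Control intention may be close to 100%.** All participants are already seeking surgery. If every control woman still intends it, halving that intention has 94% to 98% power with 15 per group. This stands, and it limits the consequence. A reader might infer from the small size that the trial can succeed only if the education all but removes the wish for surgery, or that it would miss a halving about half the time. The documents support neither. They give no control rate, and power for a halving runs from 32% to 98% over control rates of 70% to 100%, depending on the test. At a control rate of 100%, 90% power is reached with more than half the women still intending surgery. It does not rescue moderate effects, however: a 30-point drop stays below 90% power everywhere in the range, even with 17 per group.

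**The binary reading is an inference.** The primary entry joins intention with performance, questionnaire-based attitudes are also collected, and no test is assigned to the decision. This stands as a caveat. A graded intention score would have different power, but none is stated for the primary outcome, and no power is given for one.

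**The calculation may not concern the FGSIS.** Correct: the section names only genital self-image and a cited study. A reader might infer that the trial is properly powered at 90% for the FGSIS. The out-of-range mean and the figure of 10 per group speak against that. Whichever scale was used, it does not measure the primary outcome.

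**A journal article condenses.** The sample-size reasoning is nevertheless printed in full, with software, inputs, error rate, power and dropout. The point concerns what it states, not what it leaves out.

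**Conclusion.** The mismatch is plain on the face of the article and needs no outside assumption: the only power claim concerns a secondary construct and is presented as the study's. Its size does rest on assumptions, namely a binary decision, control rates of 70% to 100%, two-sided 0.05 and 15 analysed per group. On these, the trial reaches 90% power for its primary outcome only for drops of roughly 40 to 60 points, and a 30-point drop has 23% to 49% power by Fisher or 37% to 70% by chi-square. It may well detect a halving if almost all control women still intend surgery, and it probably would not if 70% do. With the printed self-image inputs, the same 15 per group gives about 98% power, so 90% describes neither outcome.

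**What to change.** Keep the decision about surgery as the primary outcome, and change the text as follows.

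- In Sample size, state that the calculation concerns genital self-image, a secondary outcome, and that the 90% does not apply to the primary outcome.
- Print the detectable difference for the primary outcome at 15 to 17 per group over a range of control rates, as in the tables above, and name the test.
- Report the primary outcome as a risk difference with an exact confidence interval, and state that a non-significant result will not be read as no effect.
- Recheck the self-image calculation: 10 versus 15 per group, and a mean of 29.09 against a 7 to 28 range. Until the source scale is reconciled, do not attribute a 90% figure to the FGSIS, and do not make it primary on the strength of this calculation.

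The cost is a less favourable stated power for the primary outcome. No added enrolment is needed. These changes disclose the low power and do not cure it.

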#### Data collection process

Attitudes toward GCS: Participants' attitudes and opinions regarding GCS will be assessed using items developed during the qualitative phase of the study. These items will provide insights into participant's perceptions and concerns regarding these procedures.

In the quantitative phase of this study, we will employ a researcher-developed questionnaire, which has been meticulously designed and validated based on the findings from the qualitative phase. After securing informed consent, we will initiate data collection using this questionnaire. The initial data will encompass participants' demographic, sexual, and reproductive characteristics. Additionally, participants will be asked to complete the standard FSFI [19] to assess sexual function and genital self-image to evaluate by using the FGSIS [20].The FSFI is comprised of 19 items categorized into six sub-domains, each assigned a specific weight or coefficient. These sub-domains include sexual desire (2 items with a coefficient of 0.6), sexual arousal and orgasm (4 items with a coefficient of 0.3 each), orgasm and satisfaction (3 items with a coefficient of 0.4 each), and pain (2 items with a coefficient of 4/0). Participants will respond on a Likert scale ranging from 0 to 5. A score of zero signifies no sexual activity within the past 4 weeks. After applying the coefficients, the overall score will fall between 2 and 36, with a lower score (FSFI ≤ 26) indicating less favorable sexual performance [21].FGSI is a 7-item patient-reported assessment tool designed to evaluate one's genital self-image. Participants rate each FGSIS item using a 4-point Likert-type scale, with options ranging from 1 (strongly disagree) to 4 (strongly agree). The individual item scores are summed to calculate the total score, falling within a range of 7–28 points. Higher total scores on the FGSIS signify a more positive genital self-image [22].The demographic profile questionnaire will encompass inquiries related to socio-economic status, including age, marital status, educational background, occupation, income, number of pregnancies and deliveries, and any history of illness or medication usage.

Furthermore, data collection will include an assessment of participants' attitudes toward undergoing GCS. The questions for this assessment were formulated during the qualitative phase of the study.

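### The sample size assumes a mean genital self-image score of 29.09 on a scale that ends at 28, so the stated 90% power is unsupported, and 15 per group does not follow from the stated inputs

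*Protocol article*

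**What the plan says.** The Sample size section (Phase III) bases the calculation on genital self-image, "considering various aspects of genital self-image", with values taken from a cited study: "M1 = 29.09, M2 = 24.11 (assuming a 20% increase due to the" intervention. The SD is 3.22 in both groups, with "a two-sided α of 0.05, and a Power of 90" per cent. From these inputs, "the sample size for each group was initially computed as 15". Then: "The final sample size for each group was established at 17 individuals to accommodate a potential 10% dropout rate". The section does not name the instrument behind these values.

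The Data collection process section (Phase III) names one genital self-image instrument, the FGSIS. It has seven items rated 1 to 4, which are summed to a total "falling within a range of 7–28 points". Higher scores mean a better self-image.

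The outcome sections list the FGSIS as secondary. The primary outcome is the intention to undergo genital cosmetic surgery or having it performed.

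**The concern.** A higher FGSIS score is better and the intervention is expected to raise it, so 29.09 must be the intervention mean. No participant can score above 28, so no group mean can reach 29.09. If the labels were reversed, 29.09 would be just as impossible as a control mean.

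This is the only power statement in the article, for a trial of 34 women. Left as it stands, a reader could take a null FGSIS result as coming from a comparison with a demonstrated 90% power, when the effect behind that figure cannot be observed on the trial's own scale. A reader could also take it to cover the primary outcome, which the calculation does not address.

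**Working it through.** **Inputs.** From Sample size: means 29.09 and 24.11, SD 3.22 in both groups, two-sided alpha 0.05, power 90%, 15 per group, 10% dropout, 17 per group. From Data collection process: 7 items, each scored 1 to 4.

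**1. The plan's own figure.**
- Difference: 29.09 − 24.11 = 4.98. Standardised effect: 4.98 / 3.22 = 1.547.
- Normal approximation: n = 2(1.960 + 1.282)² / 1.547² = 8.8, so 9 per group.
- Two-sample t-test (noncentral t): 9.85, so 10 per group.
- Power of the t-test at the stated sizes: 98.3% at 15 and 99.2% at 17.
- Variants tried: a one-sided test needs 8. Mann-Whitney needs 11 (relative efficiency 0.955) or 12 (the minimum, 0.864). The t-test at 95% power needs 12. A t-test at alpha 0.01 does give 15, but that is not the stated alpha.
- The dropout step is correct: 15 / 0.90 = 16.7, so 17.

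The stated inputs therefore do not give 15.

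**2. The means against the scale.**
- Scale maximum: 7 × 4 = 28. Excess: 29.09 − 28 = 1.09 points.
- Exact 20% increase: 24.11 × 1.20 = 28.93, also above 28.
- Printed ratio: 29.09 / 24.11 = 1.207, a 20.7% increase. This mismatch is of rounding size and nothing rests on it.
- Largest possible gain from 24.11: 28 − 24.11 = 3.89 points, against the planned 4.98.

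**3. What 15 or 17 per group delivers if SD 3.22 applies in both arms (t-test).**
- At 15 per group: 80% power for about 3.4 points, 90% for about 3.95 points. From 24.11 the second would need a mean of 28.06, just off the scale.
- At 17 per group: 90% power for about 3.69 points, a mean of 27.80.
- On a 7-28 scale, a mean m allows an SD of at most √((28 − m)(m − 7)). Setting this to 3.22 gives m = 27.49. The largest gain compatible with both 24.11 and SD 3.22 is then 3.38 points, with power 79% at 15 and 84% at 17.

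**4. What happens if the SD may shrink near the ceiling.** Normal scores with the planned means and SD were simulated, rounded, and cut off at 28 (50,000 trials). The means become about 27.2 and 23.9, and the SDs about 1.5 and 2.9. The t-test power is about 96% at 15 and 98% at 17.

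**5. What happens if the control mean is lower.** A 4.98-point difference fits on the scale if the control mean is at most 28 − 4.98 = 23.02, or about 22.5 if SD 3.22 must also hold in the intervention arm.

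**The case against.** The strongest reply is that the power may be adequate after all. A reader might infer from the impossible mean that 90% power cannot be reached in this trial. The documents do not support that. It follows only if the control mean is held at 24.11 and SD 3.22 is imposed on both arms, including one pressed against the ceiling. The limiting mean of 27.49 is reached only by a distribution with nearly every woman at 28 and a few at 7, which is no realistic guide. Cutting the planned scores off at 28 gives about 96% power at 15 per group. The 15 also has slack over the 10 that the stated inputs require. This part of the reply stands, and it limits the conclusion to power that is unsupported.

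A second reply is that the cited study may have scored genital self-image on another range, since Sample size names no instrument. That is possible and cannot be checked here. It would explain 29.09 but would not rescue the calculation: 24.11 and 3.22 would then be on the wrong scale too, and none of the inputs would carry over to the 7-28 FGSIS.

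A third reply is that the FGSIS is only secondary. That is true and limits the consequence, but the article gives no other basis for its sample size.

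**Conclusion.** The point holds in this form. The assumed intervention mean exceeds the maximum of the only genital self-image scale in the protocol by 1.09 points, and an exact 20% increase exceeds it by 0.93. The planned 4.98-point effect from 24.11 cannot occur on that scale, so the claim of 90% power has no valid basis. Separately, the stated inputs require 10 per group rather than 15, and 15 would give about 98%.

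The comparison with the scale maximum and the count of 10 rest on the protocol's own figures and a two-sample t-test, which is among the tests it lists. Every figure for actual power is conditional. It runs from 79% at 15 per group (largest gain compatible with 24.11 and SD 3.22 in both arms) to about 96% (planned scores cut off at 28), and will be lower for smaller true gains: a 10% gain of 2.41 points with SD 3.22 gives 51% at 15. The documents do not settle which applies, so neither adequate nor inadequate power should be asserted until the inputs are restated.

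**What to change.** Rewrite the Sample size paragraph:

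- Name the FGSIS as the instrument and state both means and the SD on its 7-28 scale. If the cited study used another range, rescale its means and SD first.
- Recompute from those inputs, naming the test, so that the per-group number can be reproduced.
- If enrolment stays at 17 per group with 15 analysed, state the difference that this size can detect. If SD 3.22 proves right for this scale, that is about 3.4 points for 80% power and about 3.95 for 90%, with a note that the SD shrinks near the ceiling and that from 24.11 the second figure is beyond the scale.
- Withdraw the claim of 90% power for a 20% increase.
- Say that the power statement concerns the FGSIS, a secondary outcome, and not the primary outcome of intention to undergo surgery or its performance.

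The cost is one paragraph, and the stated power may become less favourable. No extra participants are needed to restate what the fixed size delivers. Insisting on 90% power for a smaller difference could need more: 3.38 points with SD 3.22 would take 21 analysed per group.
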